### Primary and secondary outcomes

The primary outcome is self-reported knowledge, assessed as a score on a 23-item structured test covering animal reservoirs and pathogen transmission, preventive behavioural practices, disease ecology, and applied risk-reduction knowledge. Items are scored as binary variables (0/1), with a total possible score of 100, where higher scores indicate greater knowledge. The knowledge test contains single-choice and multiple-choice questions and hierarchical items, i.e., knowledge questions that are asked only if the respondent answered the previous question correctly. This adds a difficulty structure to the knowledge scale and avoids a situation in which respondents with less knowledge have fewer opportunities to get items wrong.

Secondary outcomes (self-reported) include:

Behaviour, assessed using a 9-item frequency-based scale across wildlife contact, food safety, and hygiene domains. Responses are scored on a 5-point Likert scale, with reverse coding for risk behaviours, and summed to generate a composite score (maximum 45), with higher scores indicating more protective behaviour.Attitudes, assessed using 20 Likert-scale items based on Health Belief Model constructs (susceptibility, severity, benefits, barriers, cues to action). Items are scored from 1 (strongly disagree) to 5 (strongly agree), with reverse coding for risk-promoting attitudes, yielding a total score of 100.Self-efficacy, assessed using a 7-item scale adapted from the General Self-Efficacy Scale and contextualised to zoonotic risk behaviours. Items are scored on a 4-point Likert scale (1–4), with higher scores indicating greater perceived ability to perform protective behaviours (maximum 28).Contacts (presence/absence) with zoonotic hosts are assessed as a contact matrix covering 27 animal species and multiple exposure types (e.g., proximity, handling, environmental contact), recorded as binary variables.

Socio-demographic and experiential variables are collected to describe the study population and adjust for potential confounding. The questionnaire was reviewed by experts from Thailand and Europe and piloted with a small sample (n = 24) of the target population in November 2025, in Khon Kaen Province, Thailand, to assess its clarity and feasibility. Minor revisions were made before field implementation. The questionnaire was developed based on several key publications identified through a literature review, including PREDICT project questionnaires [36,37], WHO-UNICEF WASH household survey [38], and studies on health literacy among pet owners and livestock farmers, mosquito-borne diseases, wildlife trade, and bushmeat consumption in Africa [39] and Southeast Asia [40–43]. It is divided into five sections: (1) general information and participant ID generation; (2) knowledge, attitudes, self-efficacy, and behaviour related to zoonotic disease and spillover risk; (3) exposure to animal and environmental risks across different sites usually visit (home, temple, garbage dump, water body, agricultural field, and forest) and animal contacts reported; (4) socio-demographic and livelihood characteristics; and (5) contamination and process monitoring questions.

Primary and secondary outcomes will be assessed among recruited household members in both arms during the week following completion of intervention delivery. The Village Heads will invite participants to attend the assessment interview session in the community centre. The trained trial team will obtain informed consent when it has not been obtained previously. The interview will be conducted using a structured questionnaire and will last 45–60 minutes.

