Following the village and VHV Head enrollment, we will return to the villages to explain the meeting outcomes and the study implementation to the randomly selected VHVs from the registry and obtain their agreement to participate in the study using informed consent procedures. Participating VHVs will provide information on the households they are usually responsible for, including the number of people in each household, the number of eligible adults, their ages, and names. This data will serve as a sampling frame for the random selection of seven households to participate in the trial procedures. The number of households that a VHVs regularly visits can range from 7 to 15. The data manager in the coordination site will receive a digitised list of household IDs, including the names and ages of the adults. The data manager will then randomly select seven households for participation using a pre-developed function in *R* software that facilitates random selection of the needed number from the provided sequence, i.e., 7 from n = 1–15. The data manager will provide an additional two households for replacement in case the selected household does not agree to participate. VHVs will inform them about the study and obtain verbal consent to participate in the trial.

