### Blinding criteria

Blinding will be implemented where feasible, considering the community-based nature of the intervention. Due to the design, it will not be possible to blind VHVs, participants, or the local trial team to allocation status. Outcome assessors will be blinded to the intervention allocation. Data analysts, including the statistician, principal investigator, and trial supervisors, will also remain blinded to allocation until completion of the primary analysis. The data manager will not be blinded, as access to allocation information is required for data linkage and management. Details of blinding implementation are provided in Table 1.

**Table 1 pone.0354989.t001:** Implementation of blinding in the Saan Suk cRCT (ticked box indicates blinding to the information).

Data	Local Participants and Facilitators					Local Trial Team		Trial Coordination Site Team			
	Village Head	VHV	Household head	Respondent	VHV trainers	Leading team*	Outcome assessors	Data manager	Statistician	Trial PI	Trial supervisors
District									x	x	x
Village name									x	x	x
Village location, address									x	x	x
Village Head name									x	x	x
House address									x	x	x
Household head name									x	x	x
Respondent name									x	x	x
VHV name									x	x	x
Generated District ID	x	x	x	x	x		x				
Generated Village ID	x	x	x	x	x		x				
Generated Household ID	x	x	x	x	x		x				
Generated Respondent ID	x	x	x	x	x		x				
Village Health Volunteer ID	x	x	x	x	x						
Intervention allocation							x		x	x	x
Masked allocation	x	x	x	x	x		x				

*Leading team in Thailand: field supervising manager, leading investigators from Khon Kaen University.

Routine unblinding will not occur during the trial. All outcome assessments and primary statistical analyses will be conducted with masked allocation, and the study database will remain blinded until database lock and completion of the prespecified primary analyses. Unblinding before database lock will be permitted only under exceptional circumstances in which knowledge of intervention allocation is required for ethical, regulatory, or legal reasons.

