### Informed consent

We will obtain informed consent from four groups: Village Heads, Village Health Volunteers (VHVs, including VHV Heads), Household Heads, and adult household members selected for the outcome assessment. All individuals will receive a participant information sheet and will have the opportunity to ask questions before providing consent. Informed consent from Village Heads, VHV Heads, and VHVs will be obtained by the research team before the allocation of interventions. Village Heads will provide consent for their villages to participate in the study before randomisation. In the intervention arm, household members will provide informed consent before the intervention implementation. In the control arm, individuals participating in the outcome assessment will be asked to provide informed consent before the procedure.

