We acknowledge that the implementation of the Saan Suk programme depends on the availability, motivation, and capacity of VHVs. VHVs are trusted community actors well placed to deliver household-level health education interventions; however, they may differ in experience, communication style, time availability, and confidence in delivering One Health content. To support intervention fidelity, VHVs in the intervention arm will receive standardised training during a two- to three-day workshop, including a manual, structured materials, and communication training. Adherence and fidelity will be monitored through visit documentation, conducted by VHVs and evaluated by the trial coordination team.

Village Heads will also play an important role in supporting trial implementation, including encouraging adherence to training and field procedures. Their involvement in the allocation process, including the public envelope draw, is intended to strengthen transparency, community acceptance, and local ownership. Village Head permission is necessary for the respective village participation in the study; however, individual informed consent will also be obtained from trial participants, including VHVs and adult household members, where they participate in study-specific procedures or outcome assessment.

Outcome assessment is based on self-reported information, including knowledge, attitudes, self-efficacy, behaviours, and contacts with local animal hosts. These outcomes are appropriate for evaluating behavioural determinants of zoonotic spillover prevention, but they are subject to self-report and social desirability bias, particularly after delivery of an educational intervention [44]. To reduce measurement bias, outcome assessors will be trained, standardised questionnaires will be used, and outcome assessment teams will remain blinded to the intervention allocation. The questionnaire was expert-reviewed, back-translated, and piloted in the target communities to improve clarity, cultural appropriateness, and acceptability. The questionnaire also includes items to collect information on potential baseline factors that may differ between the trial arms and, if necessary, can be adjusted for in the analysis. Non-self-reported outcomes of zoonotic disease prevention behaviour or spillover risk are not feasible within the scope of this trial.

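### Assessor blinding is predictably compromised: individual consent is timed differently by arm, and contamination questions sit in the same interview as the outcomes

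*Protocol article*

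**What the plan says.** On blinding, the section Blinding criteria states: "Outcome assessors will be blinded to the intervention allocation". The Discussion lists this among the measures against measurement bias, saying that "outcome assessment teams will remain blinded to the intervention allocation".

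On consent, the section Informed consent sets a different time for each arm: "In the intervention arm, household members will provide informed consent before the intervention implementation", whereas "In the control arm, individuals participating in the outcome assessment will be asked to provide informed consent before the procedure". The section Primary and secondary outcomes adds, for the assessment session in the community centre: "The trained trial team will obtain informed consent when it has not been obtained previously".

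Other parts describe consent without distinguishing the arms. Under Recruitment, "VHVs will inform them about the study and obtain verbal consent to participate in the trial", and Table 2 schedules this verbal household consent in weeks 2 and 3. The section Participants requires written consent from each adult household member.

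On the questionnaire, Primary and secondary outcomes lists five sections. Knowledge, attitudes, self-efficacy and behaviour form the second; the last is "5) contamination and process monitoring questions". The Data management plan says that assessors will be trained to use standard wording that does not mention the intervention.

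**The concern.** Allocation is by village, so anything that reveals the arm for one respondent reveals it for everyone interviewed in that village. Two routine steps in the plan can do this.

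The first is consent. If the arms consent at different times, a person running the assessment session can infer the arm from whether consent forms still have to be signed. This happens before the knowledge test.

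The second is the contamination and process section. Its purpose is to find out who was exposed to the programme. Neutral wording controls what the assessor says, not what the respondent answers.

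The primary outcome and all secondary outcomes come from the same interviewer-administered questionnaire, outcomes are not measured at baseline, and respondents cannot be blinded. Assessor blinding is therefore one of the few protections against measurement bias that the design has.

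**Working it through.** The plan states no figure on this point, so the check sets the provisions side by side and then gives a scale.

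**1. Consent status by arm at the session**

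| | Intervention villages | Control villages |
|---|---|---|
| Individual consent due (Informed consent) | before delivery | at the outcome assessment |
| Position at the session, if the plan is followed | on file | outstanding |
| Action at the session (Primary and secondary outcomes) | none | trial team obtains consent |

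Consent status therefore separates the arms by default, ahead of the knowledge items. Two things weaken the cue. Some intervention members may consent late and sign at the session. The verbal household consent taken by Village Health Volunteers (VHVs) covers both arms, so control members will have agreed to something earlier. That verbal step does not remove the cue, because written individual consent is also required and its timing is set by arm.

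**2. Who would see the cue**

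The article says that the trained trial team takes outstanding consent. It does not say whether these people are also the assessors, and it assigns neither consent nor the fifth questionnaire section to other staff. Table 1 leaves assessors unmasked to village name, so they can carry what they learn from one respondent to the next.

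**3. Contamination and process section**

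It is listed last. If the sections run in order, it cannot affect the same respondent's knowledge score; it can only inform later interviews in that village. With 42 respondents per village:

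- One assessor, or a team that shares what it hears: up to 41/42 = 97.6% of interviews follow the first disclosure.
- Six assessors in parallel who share nothing (an assumption, for illustration): (42 − 6)/42 = 36/42 = 85.7%.

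Parallel interviewing is plausible: 42 interviews of 45 to 60 minutes take 31.5 to 42 assessor-hours per village. Both percentages assume that each assessor's first respondent discloses the arm, so both are upper bounds for their setting.

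**4. Scale of the outcome**

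- Target difference: d × SD = 0.40 × 15.23 = 6.09 points, which agrees with the protocol's approximately six.
- One item, assuming equal weights: 100/23 = 4.35 points.
- One item relative to the target: 4.35/6.09 = 71%.
- Items equal to the whole target: 6.09/4.35 = 1.40.

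An average between-arm shift of 1.4 items would thus equal the whole target effect. This shows how coarse the scale is. It does not estimate bias, because the documents give no rate at which an unblinded assessor would prompt or score differently.

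**The case against.** The strongest reply is that the text does not show assessors taking consent. The article speaks of a trained trial team there and of outcome assessors elsewhere, and the unblinded leading team could run the consent desk. Staffing of that kind is often left to the full protocol, which is not shown. This stands as a limit: the documents do not prove that assessors will learn the arm. It does not remove the point, because the timing of consent by arm is stated, and nothing stated shields assessors from it.

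A second reply is that the items are single- or multiple-choice, scored 0/1 and entered electronically with validation checks, which limits discretion. This also stands in part. Less room for discretion is not none: some items are asked only after a correct answer to the one before, and the protocol itself treats blinding as a needed safeguard.

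A reader might infer more than the documents support:

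- *That blinding is abolished, or that only control respondents still need consent.* The instruction on outstanding consent names no arm, and late consent in intervention villages is possible.
- *That at least 41 of 42 interviews per village are unblinded.* That figure is an upper bound.
- *That the contamination section certainly reveals the arm.* Its items are not shown.
- *That the blinding section contradicts itself.* It says that "it will not be possible to blind VHVs, participants, or the local trial team to allocation status", and Table 1 places assessors under the local trial team. But the next sentence exempts assessors, and Table 1 gives them their own column, marked as blinded to allocation. This is loose grouping.
- *That the bias can be expressed as a share of the target effect.* This would need an invented rate of favourable scoring.

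**Conclusion.** The concern holds in this form: by its own default procedures, the plan makes it likely that assessors can infer a village's arm, which undermines the blinding it states and relies on. The consent route is the firmer of the two. It follows from stated text, precedes the knowledge test, and assumes only that assessors can see whether consent is being taken. The contamination section is a likely second route, for later interviews in the same village only, and is an inference about unseen items.

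The size of any bias is unknown. The 4.3 points per item (equal weights assumed) against a target of about 6 show that small differences in questioning or recording could matter, not that they will occur. Because the remedy is cheap and no participants had been enrolled at submission, the change should be made.

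**What to change.** 1. Obtain individual written consent at the same time and in the same way in both arms, during the household enrolment already scheduled for weeks 2 and 3. Reconcile Recruitment, Informed consent, Primary and secondary outcomes, and Table 2, which now differ on whether this consent is verbal or written, who takes it, and when.
2. Have any consent still outstanding at the session taken by existing unblinded field staff who do not assess outcomes, and say so in the protocol.
3. Administer the contamination and process section separately from the outcome interview, either by such non-assessor staff or after all outcome interviews in the village are complete.

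The cost is a modest change to workflow and scheduling: written consent in control villages moves several weeks earlier, non-assessor staff must be available at each session, and respondents have a short second step. Design, sample size and analysis are unaffected. Respondents may still volunteer their village's arm during the interview; these steps remove only the cues that the plan itself creates.

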### Data management plan

Outcome assessment data will be collected electronically in the field using the Lime Survey platform and securely stored on password-protected servers hosted by Heidelberg University, Germany. Outcome assessors will receive standardised training covering interview techniques, use of electronic data collection tools, ethical conduct, and neutral communication procedures. Training will emphasise the use of standardised wording to avoid any reference to intervention, thereby measuring potential contamination between the arms. Built-in validation checks (e.g., range checks, skip logic, mandatory response fields, and outlier and unusual values) will be embedded in the electronic data collection system. Where internet connectivity is limited, paper-based forms will be used temporarily and subsequently entered into the electronic system following secure data transfer procedures.

Unique identification codes will be assigned to participants, VHVs, and villages. A linkage (key sequence) file connecting identifiers to personal information will be stored separately in a secure, access-restricted location and maintained by the data manager. Data quality will be ensured through built-in validation checks within the electronic data capture system, daily monitoring of incoming data, and periodic review of completed records by the data manager and the field team. The data manager will oversee data cleaning, coding, and verification across all datasets, including quantitative data during the ongoing outcome assessment. Data management and confidentiality procedures will follow institutional and General Data Protection Regulation (GDPR)-compliant standards for the collection, storage, processing, and archiving of personal and research data.

All personal information collected during the trial will be handled in accordance with strict confidentiality procedures before, during, and after the study. Participant data will be pseudonymised at the point of collection using unique study identification codes, and identifiable information (e.g., name and contact information) will be stored separately from research data in secure, access-restricted systems. Only authorised members of the trial coordination team will have access to the linkage file.

All electronic data will be stored on secure, password-protected servers hosted by Heidelberg University. Access will be restricted based on user roles. Paper-based materials, including consent forms, will be stored in locked cabinets at Khon Kaen University, Thailand. All analyses, reports, and publications will use aggregated or anonymised data. No individual participants will be identifiable in any dissemination outputs, including publications, presentations, or any other dissemination materials. All study data will be retained for up to 10 years in accordance with institutional archiving policies and then securely destroyed.

The coordinating centre for the Saan Suk trial is based at the University Hospital Heidelberg (UKHD), Germany, with operational support from Khon Kaen University (KKU), Thailand (Local trial team). UKHD is responsible for overall trial coordination, including regulatory management, ethics approvals, data systems, statistical analysis, and quality monitoring. At the same time, KKU leads day-to-day field implementation and documentation, including coordination with Village Heads and VHVs, scheduling of field activities, training, and engagement with local authorities. A central trial management team comprising researchers and field officers from UKHD and KKU will meet regularly to review progress and coordinate activities.

This trial does not involve a formal data monitoring committee, as Saan Suk is a minimal-risk, behavioural intervention with no clinical dosing, radiation, or invasive procedures. Therefore, no formal interim effectiveness analyses are planned, and anticipated harms are primarily social or operational. Consistent with risk-proportionate oversight, an independent Trial Steering Group (TSG) will provide external monitoring of safety, data quality, contamination, and trial conduct. TSG members who are not involved in intervention delivery or data collection will receive masked, de-identified reports (clusters labelled A/B) and may request unmasking only in exceptional circumstances (e.g., for safety reasons), which will be documented in the minutes.

### Safety considerations

This is a minimal-risk, education-based intervention. Physical medical risks are minimal, the primary foreseeable social or psychological risks (e.g., conflict, stigma, or distress) are minimal; and safety concerns during or after visits (e.g., dog bites while approaching homes) and travelling to the meetings. The intervention trial arm will be monitored through developed adverse event logs.

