As this trial involves a non-clinical educational intervention, no medical risks are anticipated. However, criteria are defined for discontinuing or modifying the allocated intervention at the individual, provider, and trial levels. For households and individuals, we will discontinue (stop all remaining study visits for that household) if any of the following occur: (1) participant or household head requests to stop participation at any time, for any reason (no justification required); (2) any safety event during or within 24 hours after a visit that poses immediate risk to the participant, household member, or VHV (e.g., physical aggression, threats, severe dog bite or animal attack, hazardous environment); (3) serious adverse event plausibly related to the visit (e.g., injury while acting on a demonstration); (4) confidentiality concern that cannot be mitigated; and (5) loss of eligibility, such as when a participant moves away or lacks capacity to consent. Discontinuation may also occur following a request from VHVs, community leaders, or local authorities. At the VHV level, the intervention delivery will be discontinued if any of the following occur: (1) the VHV fails competency checks after training, (2) breaches confidentiality, or (3) is implicated in a safety-related complaint. In such cases, households will be reassigned to another trained VHV within the same village where feasible. If reassignment is not possible, the intervention will be modified (e.g., delivered in leaflet-only format by a supervisor) or discontinued, and this will be documented as a delivery limitation rather than a crossover.

At the trial level, cRCT may be discontinued (1) in case of major logistical, environmental, political, and civil unrest barriers preventing continuation of the study procedures, (2) ethical or safety concerns raised by the Ethics Committee or relevant authorities, or (3) external events such as natural disasters or public health emergencies that make study implementation unsafe. Discontinuation may also occur if there is (4) an inability to enrol or retain clusters or participants at a sufficient rate to ensure trial completion, (5) loss of implementing partners or VHV network capacity, or (6) data quality failure compromising interpretability, such as when more than 20–30% of primary outcome data are missing.

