**INTERVENTION IMPLEMENTATION:**												
*Intervention arm*												
Training of the trainers			x									
Trainers train VHVs				x								
VHVs conduct community meetings				x	x							
VHVs conduct household visits for intervention sessions						x	x	x	x			
*Control arm*												
VHV conducts household visits as standard practice					x	x	x	x	x			

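### Adverse event logs are assigned to the intervention arm and none is described for control villages, so harms can be described for one arm only, which fits poorly with masked A/B safety reports

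*Protocol article*

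**What the plan says.** The Safety considerations section calls the trial minimal-risk. It names social or psychological harms (conflict, stigma, distress) and also "safety concerns during or after visits (e.g., dog bites while approaching homes) and travelling to the meetings". It then says: "The intervention trial arm will be monitored through developed adverse event logs". It gives no matching arrangement for the control arm.

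Table 2 lists, for the control arm, "VHV conducts household visits as standard practice", marked for weeks 4 to 8. Intervention visits are marked for weeks 5 to 8. Under Primary and secondary outcomes, participants in both arms are invited to an interview session at the community centre.

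On oversight, the Data management plan says "This trial does not involve a formal data monitoring committee" and instead that "an independent Trial Steering Group (TSG) will provide external monitoring of safety, data quality, contamination, and trial conduct". Members of that group "will receive masked, de-identified reports (clusters labelled A/B) and may request unmasking only in exceptional circumstances".

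The discontinuation criteria under Intervention and comparator include "any safety event during or within 24 hours after a visit that poses immediate risk to the participant, household member, or VHV". This is a rule for stopping visits to a household, not a rule for recording events in both arms.

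**The concern.** Most of the harms named come from someone approaching a home, from friction or distress around a visit, or from travel. They are not specific to the Saan Suk content. Control villages share the visits and the journey to the interview. If events are recorded in one arm only, the trial gives up the comparison that randomisation would otherwise provide almost free: events during Saan Suk visits against events during usual visits. That comparison has some value, because the programme is meant to be proposed for the national VHV training if it proves effective.

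The second issue is consistency. The Steering Group is the only independent body described with a safety remit, and its reports are meant to be masked. A log kept for one arm does not fit easily with safety reporting by masked label.

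**Working it through.** The protocol states no figure on harms, so there is none to reproduce. The check is a reading of every place where events, logs or masking appear, followed by one illustrative calculation.

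**1. Which logs exist, and for whom**

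- Adverse event logs (Safety considerations): intervention arm named, control arm not mentioned.
- VHV activity logs (Intervention and comparator): visits, dates and observations, kept to monitor intervention delivery.
- Activity logs by the coordination team, and reasons for non-response or discontinuation recorded by field teams (Discussion): not described as adverse event records.
- Protocol deviation log (Ethical considerations): not an adverse event record.

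None of these is an adverse event record for control villages.

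**2. Can the named harms occur in control villages?**

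| Harm named | Intervention arm | Control arm |
|---|---|---|
| Dog bite or similar at a visit | Yes, visits in weeks 5–8 | Yes, visits in weeks 4–8 |
| Conflict, stigma or distress | Yes | Possible, from visits and interview |
| Travel | Community meetings and interview session | Interview session |

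Exposure is not identical, since the VHV-led community meetings are listed for the intervention arm only, but every type of harm has a control-arm counterpart.

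**3. What can be estimated**

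A difference or ratio in harms needs a numerator from each arm. The control denominator is known: 12 villages × 42 = 504 people. The control numerator is not collected. It is missing and should not be read as zero.

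**4. Consequence for masking**

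If (a) only intervention villages can contribute events and (b) events are tabulated by A/B label, then one event under a label identifies that label as the intervention arm. If events are pooled across labels, they do not reveal allocation.

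**5. How likely is at least one logged event?**

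Planned intervention visits: V = 12 villages × 42 households (6 VHVs × 7 households) × 4 weekly visits = 2,016.

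P(at least one event) = 1 − (1 − r)^2016, where r is the event rate per visit. The protocol gives no rate, so r is assumed:

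| Assumed r per visit | P(at least one event) |
|---|---|
| 0.0001 | 18% |
| 0.0005 | 64% |
| 0.001 | 87% |
| 0.005 | >99.9% |

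This treats visits as independent. Events that recur in the same household would lower the figures; events outside visits, such as during travel, would raise them.

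**The case against.** The best case for the plan is as follows.

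- The text does not say that logging is confined to one arm. The safety section is short, and the article condenses a fuller protocol. This stands in part: the restriction is inferred. But the article does more than stay silent. It names one arm of a two-arm trial as the one to be monitored.
- No safety outcome, hypothesis or between-arm harms analysis is promised, and concentrating on the added activity is defensible in a minimal-risk educational trial. This stands. No stated objective is contradicted, which is why the point is modest.
- The Steering Group neither measures nor analyses outcomes, is not listed in the blinding table, and may request unmasking for safety reasons. No interim effectiveness analysis is planned. This also stands.
- Symmetric logging may not secure the mask. Contamination data, also in the group's remit, or an event narrative that mentions a demonstration could still hint at allocation. This stands.
- Asking about events at the outcome interview could lead participants to describe their visits to assessors who must stay blinded. This is a real risk, and the fix has to avoid it.

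Three stronger readings are tempting but unsupported. A reader might infer that the Steering Group will be unmasked as soon as any event is reported. That needs events to be tabulated by label, which the Data management plan implies but does not state. A reader might also infer that the criterion for stopping visits after a serious event plausibly related to a visit cannot work without a control background rate. That criterion is an individual causal judgement about one household, and its example is an injury while acting on a demonstration. Finally, a reader might infer bias in the knowledge comparison. Nothing in the safety arrangements touches how the primary outcome is collected or analysed.

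**Conclusion.** The point holds in a limited form. Followed as written, the protocol yields a description of harms for the intervention arm and no corresponding record for the control arm, so the two cannot be compared. The safety section and the A/B-masked reporting also need to be reconciled. Loss of the Steering Group's masking is conditional on events being shown by label. Given that, its probability depends on an event rate the document does not give: 18% to 87% for assumed rates of 0.0001 to 0.001 per visit. The conclusion rests on reading the naming of one arm as excluding the other. The primary estimate is unaffected. This is an inexpensive improvement to make before recruitment, not a flaw in the main comparison.

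**What to change.** Use the existing adverse event log in both arms, with the same event definitions, reporting window and prompts. VHVs in both arms would complete it. Control VHVs do not attend the Saan Suk training, so they would need brief separate instruction that contains no programme content. Completed logs should go to unblinded field staff or the data manager and should not be collected by the blinded outcome assessors. Report events to the Steering Group by masked label with village-level denominators, and keep wording that reveals the arm out of the event narratives.

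If two-arm recording is not wanted, say so: state that harms are described for the intervention arm only, and that events in Steering Group reports are either pooled across labels or not masked.

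The cost of the first option is a small reporting and instruction burden for control VHVs; the form already exists, and no participants had been enrolled at submission. It removes one route to unmasking, not all of them, because contamination data or narratives may still hint at allocation. The second option costs only a change of wording, but gives up the comparison.
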